Aquatic exercise is highly recommended because of its numerous benefits to the human body through the use of the water’s buoyancy, which can help decrease body fat while maintaining superior stability compared with ground exercises [15]. The deep water running in interval training (DWR-IT) is a new approach in the field of aquatic exercise to control obesity and aims to increase energy expenditure, improve cardiovascular fitness, and reduce body fat percentage [16].

DWR-IT is an aquatic aerobic exercise performed in relatively deep pools and consists of simulated running while wearing a floatation vest, which serves to keep the body in an upright position and helps to prevent contact between the feet and the bottom of the pool [17]. The main advantages of the DWR-IT technique are buoyancy and lack of weight-bearing, minimizing the repeated stress and impact experienced in running on land, and low risk of musculoskeletal injuries. In addition, the individual can perform the same amount of work intermittently and with the same intensity as continuous exercise; however, the degree of fatigue after interval training is considerably smaller and more pleasant for this population [18].

However, little is known about the chronic effects of DWR-IT performed in a heated pool (32 °C), in the body composition evaluated by electrical bioimpedance and functional capacity measured by the six-minute walk test (6MWT) in overweight and middle-aged obese.

Given the above, the proposal of the present study for the advancement of scientific knowledge in the area of aquatic training and rehabilitation in overweight and obese women becomes relevant. Accordingly, the objective of the study will be to investigate the effect of the DWR-IT program on the body composition, functional capacity, and quality of life of overweight adults.

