#### Sample size

The sample size was performed on the basis of a pilot study, conducted previously with middle-aged women submitted to a DRW protocol [32]. Sample size calculation was performed by using G*Power version 3.1 software (Heinrich-Heine-Universität Düsseldorf, Düsseldorf, Germany). The maximum distance covered in 6MWT assessed before (566.2 ± 51.8 m) and after (625.1 ± 73.6 m) the DWR program was considered the main outcome. Significance level was set at 5% with 80% power. A sample of 12 participants per group was suggested. Given a possible 20% dropout rate, 15 participants will be required per group, thus totaling 30 participants.

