#### Analysis

The normality and homogeneity of data variance will be verified through the Shapiro–Wilk and Levene tests, respectively. For the variables with normal distribution, the two-way mixed-design analysis of variance (ANOVA) test (a repetition factor and a group factor), followed by Bonferroni post hoc, will be applied. For variables with non-normal distribution, the Wilcoxon tests will be used to compare the differences between times and the Mann–Whitney test to compare differences between groups. In this case, the Bonferroni adjustment will be used *a priori*. In all tests, the significance level of 5% will be considered. The effect size will be calculated by using Cohen’s d, and the results interpreted on the basis of Cohen as follows: small (0.21–0.49), medium (0.50–0.79), or large (≥0.80) [33].

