This study presents some strengths that in previous studies were not considered, such as the presence of the control group and use of specific instruments for the obese population. For the prescription of exercise intensity in the aquatic environment should take into account the help of HR for the prescription of intensity in the aquatic environment, thus avoiding cardiovascular overloaded of the control group, use of specific instruments for the obese population.

Therefore, the present study will provide clinical evidence that the DWR-IT program is effective in improving functional capacity, muscle strength, sleep quality, and quality of life in the obese. Thus, DWR is an alternative aquatic exercise to be considered by professionals in order to develop effective interventions for adults with obesity.

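### Every outcome is tested at 5% and the efficacy conclusion is not tied to the named main outcome (6MWT), so the risk of a false efficacy claim in some domain is inflated

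*Protocol article*

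**What the plan says.** All references are to the protocol article.

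- **Background, last paragraph.** The objective is "to investigate the effect of the DWR-IT program on the body composition, functional capacity, and quality of life of overweight adults". The three domains are not ranked, and the Discussion repeats them unranked.
- **Abstract, Discussion.** Target improvements are given for body fat, the 6MWT and four IWQOL-LITE domains, again without order.
- **Sample size.** Distance in the 6MWT, "assessed before (566.2 ± 51.8 m) and after (625.1 ± 73.6 m) the DWR program was considered the main outcome". The design figures follow: "Significance level was set at 5% with 80% power", then "A sample of 12 participants per group was suggested".
- **Analysis.** Normally distributed variables go to a two-way mixed ANOVA with Bonferroni post hoc tests. Other variables go to Wilcoxon tests between times and Mann–Whitney tests between groups, with a Bonferroni adjustment set in advance whose family is not stated. Then: "In all tests, the significance level of 5% will be considered". The 6MWT is not mentioned here, and no ANOVA term is named as the one that decides efficacy.
- **Discussion, closing paragraphs.** "the present study will provide clinical evidence that the DWR-IT program is effective in improving functional capacity, muscle strength, sleep quality", and quality of life is added to that list. The sentence is not conditional on any result.

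**The concern.** The main outcome has a name in one section and no role in the two that matter for inference: the section that sets the tests and the section that states the conclusion. The claims also shift. The objective covers body composition, functional capacity and quality of life; the closing Discussion drops body composition and adds muscle strength and sleep quality. The set of confirmatory claims is therefore not fixed.

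At stake is how a positive report could be read. With 30 participants and many outcomes each tested at 5%, a chance result on one questionnaire domain could be presented as evidence of effectiveness even if the 6MWT showed no difference. Nothing in the Analysis section or the Discussion rules that out.

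**Working it through.** **1. The plan's own figure.** The pilot 6MWT change is 625.1 − 566.2 = 58.9 m. The pre-post correlation is not given; assume 0.5.

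- SD of change = √(51.8² + 73.6² − 2 × 0.5 × 51.8 × 73.6) = √4287.7 = 65.5 m
- Standardised change = 58.9 / 65.5 = 0.90
- A paired two-sided t-test at 5% with 80% power needs n = 11.8, so 12 (power 80.9% at 12)
- Dropout: 12 / 0.80 = 15 per group, 30 in total

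The stated 12 and 15 are reproduced, and the sample size rests on the 6MWT alone at 5%. They are reproduced as a before-after comparison within one group, so this section does not settle which comparison decides efficacy either.

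**2. Number of outcomes, from the Procedures section.**

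| Domain | Variables | Count | In the Discussion's claim |
|---|---|---|---|
| Functional capacity | 6MWT | 1 | yes |
| Muscle strength | chair stand, arm curl | 2 | yes |
| Sleep | PSQI, ESS | 2 | yes |
| Quality of life | five IWQOL-LITE domains | 5 | yes |
| Body size and composition | body mass, BMI, abdominal circumference, body fat | 4 | no |

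This gives 10 variables in the claimed domains and 14 in all. The food frequency and physical activity questionnaires are left out because the Control group section uses them for monitoring. The count is a reconstruction; the figures showing the assessment schedule are not available.

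**3. What the Bonferroni statements cover.** After the ANOVA, the correction is post hoc and so applies to contrasts within one outcome. In the non-parametric branch the family is undefined. If it does span outcomes there, non-normal variables would be protected and normal ones would not, so protection would depend on the Shapiro–Wilk result.

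**4. Chance of at least one false favourable result.** Suppose there is no effect on any outcome. Each two-sided 5% test is then significant in the favourable direction with probability 0.025.

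- Independent outcomes: 1 − 0.975^k. For k = 10: 1 − 0.975^10 = 0.224. For k = 14: 1 − 0.975^14 = 0.298.
- Common correlation ρ: 1 − ∫ φ(w) Φ((1.96 − √ρ·w)/√(1 − ρ))^k dw, evaluated numerically.

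| Assumed ρ | 10 variables | 14 variables |
|---|---|---|
| 0 | 22% | 30% |
| 0.3 | 18% | 22% |
| 0.5 | 14% | 17% |
| 0.7 | 11% | 12% |

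For one test the figure is 2.5%, so the inflation is roughly 4-fold (10.7 / 2.5 = 4.3) to 12-fold (29.8 / 2.5 = 11.9).

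**5. For comparison, errors in either direction.** 1 − 0.95^14 = 0.512 and 1 − 0.95^10 = 0.401 under independence. At ρ = 0.7 they fall to 25% and 21%.

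**The case against.** The strongest reply is that a hierarchy already exists. The Sample size section names one main outcome and sizes the trial on it at 5%, so the error rate for that outcome is 5%, and testing secondary outcomes at 5% without adjustment is common. The article is also condensed, and the multiplicity family is usually defined in the analysis plan.

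Much of this stands. The 6MWT is named, and an undefined family alone would not be a finding. But the article does more than stay silent: it sets 5% for every test and announces efficacy in four domains. Holding the 6MWT at 5% does not protect claims on strength, sleep and quality of life.

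Three stronger readings are tempting and not supported:

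- **That any one significant outcome will count as efficacy.** No section says so. The Discussion sentence is an over-confident forecast over four domains, not a decision rule. The figures above are conditional on such a reading.
- **That a false efficacy claim is likely, at 51%.** That needs 14 independent outcomes with no effect on any of them, and counts harmful as well as favourable results. Independence is implausible: BMI is computed from body mass, and five variables come from one questionnaire.
- **That no adjustment across outcomes exists anywhere.** For the non-parametric branch the text is ambiguous, not shown to be confined to one outcome.

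**Conclusion.** The point holds in a limited form. The main outcome is named but not carried into the testing rule or the conclusion, the deciding comparison is not stated, and adjustment across outcomes is absent or undefined, while efficacy in four domains is announced in advance.

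The risk of a false favourable result is substantially inflated, to about 11% to 22% for the claimed variables and 12% to 30% for all 14, against 2.5% for one test. This rests on no true effect on any outcome, a common correlation between 0.7 and 0 (assumed), two-sided tests (sidedness is not stated), no cross-outcome adjustment in either branch, and a reader accepting any favourable result as efficacy. It should be corrected before analysis; it does not invalidate the trial.

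**What to change.** 1. In the Analysis section, state that the between-group difference in 6MWT change at week 12 (the group-by-time effect) is the single confirmatory test, at two-sided 5%, and that the efficacy conclusion rests on it.
2. Report all other outcomes as secondary, with estimates and 95% confidence intervals and no stand-alone efficacy claim. A multiplicity adjustment such as Holm is optional.
3. Define the family to which each Bonferroni adjustment applies.
4. Make the closing Discussion sentence conditional on the results.

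**Cost.** These are wording changes and leave the planned 30 participants unchanged. The price is that secondary outcomes lose confirmatory status. The alternative of keeping all 14 confirmatory with Bonferroni is much dearer: 0.05 / 14 = 0.0036 per test, which raises the paired requirement from 12 to about 22 and a two-group comparison on the pilot values from about 20 to about 36 per group.

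A separate matter, not caused by this fix but made visible by it: on the pilot values a between-group comparison has about 58% power at 12 per group.

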### Randomization and allocation

Randomization will be performed after baseline assessments. Sequentially numbered opaque sealed envelopes will be prepared ahead of time and randomly assigned by a computer-generated table of random numbers in a 1:1 proportion. A person blinded to the study protocol will perform the randomization and provide the group assignment to the treating physical therapist. Volunteers will be allocated to the water group, which will be submitted to the 12-week DWR-IT program, or to the control group, which will not be submitted to intervention and will be instructed not to engage in any kind of structured physical exercise training and to keep the life activities identified at baseline. The International Physical Activity Questionnaire (IPAQ) will be applied before and after the intervention in order to assess the level of physical activity. Failure to follow the recommendations is an exclusion criterion in the study (Fig. 2).

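### Effect sizes are to be labelled small, medium or large from the point value of Cohen's d, which at 12 to 15 per arm is too imprecise for small and medium labels to carry much information

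*Protocol article*

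**What the plan says.** The Analysis section of the protocol article plans a two-way mixed ANOVA with Bonferroni post hoc comparisons for normally distributed variables. Other variables go to Wilcoxon and Mann–Whitney tests with a Bonferroni adjustment. All tests use the 5% level. The section then adds: "The effect size will be calculated by using Cohen’s d", "and the results interpreted on the basis of Cohen as follows". The bands are 0.21 to 0.49 for small, 0.50 to 0.79 for medium and 0.80 or more for large. The rule is general and attaches to the value of d itself.

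The Sample size section fixes the precision available: "A sample of 12 participants per group was suggested", and then "Given a possible 20% dropout rate, 15 participants will be required per group, thus totaling 30 participants". Allocation is 1:1 (Randomization and allocation).

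**The concern.** A verbal size label on a point estimate is useful only if the estimate is precise enough to separate one band from the next. The bands here are about 0.3 wide. With 12 to 15 per arm, the 95% CI for a between-arm d is about 1.5 to 1.6 wide, so it spans several bands and usually zero as well.

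What is at stake is the wording of the report. The trial measures many outcomes: body fat, 6MWT, five IWQOL-LITE domains, PSQI, ESS, chair stand and arm curl already make eleven. If the rule is followed as written, some of them can be expected to be called medium or larger by chance, next to a negative test. The section gives no rule for reconciling the two.

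**Working it through.** **Inputs.** Per-arm n of 12 (evaluable) and 15 (enrolled), from Sample size; the second follows from the first, 12 / (1 - 0.20) = 15. Allocation 1:1. Cut-offs 0.21, 0.50 and 0.80 and the 5% level, from Analysis. The article does not define d, so the main calculation assumes the usual between-arm d, scaled by the same SD as the test.

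**1. Labels when there is no true effect.** With n per arm, d = t × sqrt(2/n), so P(|d| ≥ c) = 2 × P(T > c × sqrt(n/2)) with 2n - 2 degrees of freedom. The multiplier sqrt(n/2) is 2.449 for n = 12 (22 df) and 2.739 for n = 15 (28 df).

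| Label | n = 12: t, probability | n = 15: t, probability |
|---|---|---|
| small or larger (0.21) | 0.514, 61.2% | 0.575, 57.0% |
| medium or larger (0.50) | 1.225, 23.4% | 1.369, 18.2% |
| large (0.80) | 1.960, 6.3% | 2.191, 3.7% |

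These count both directions. In favour of the water group only, small or larger has probability 30.6% (n = 12) and 28.5% (n = 15). Over eleven outcomes with no true effect, the expected number labelled medium or larger in either direction is 11 × 0.234 = 2.6 at 12 per arm and 11 × 0.182 = 2.0 at 15.

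**2. How the label varies with the truth.** Noncentral t, n = 12, either sign:

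| True d | none | small | medium | large |
|---|---|---|---|---|
| 0 | 38.8% | 37.8% | 17.1% | 6.3% |
| 0.20 | 34.8% | 36.6% | 19.4% | 9.2% |
| 0.35 | 27.7% | 33.8% | 23.1% | 15.4% |
| 0.50 | 19.6% | 29.1% | 26.5% | 24.8% |
| 0.93 | 3.7% | 11.2% | 22.6% | 62.5% |

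The small label is about as likely with no effect as with a true d of 0.35. The large label does separate no effect from a large one.

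**3. Intervals and significance.** An observed d of 0.50 has a 95% CI, by inversion of the noncentral t, of -0.32 to 1.31 at n = 12 and -0.23 to 1.22 at n = 15. The smallest |d| significant at two-sided 5% is t(0.975, 2n - 2) × sqrt(2/n): 2.074 × 0.408 = 0.85 at n = 12 and 2.048 × 0.365 = 0.75 at n = 15. On this definition every small label is non-significant. So is every medium label at 12 per arm, and every medium label below 0.75 at 15.

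**4. Sensitivity to the definition of d.** The pre-post correlation r is not in the article, so a range is shown. Rates are for small or larger with no true effect; the first figure of each pair is n = 15, the second n = 12.

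| Assumed r | difference in change / baseline SD | within-arm d |
|---|---|---|
| 0.5 | 57–61% | 42–48% |
| 0.7 | 46–51% | 31–36% |
| 0.8 | 37–42% | 22–27% |
| 0.9 | 21–26% | 9–13% |

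If the difference in change is divided by the SD of change, the rates stay at 57–61% whatever r is. If it is divided by baseline SD, the significance threshold is multiplied by sqrt(2(1 - r)). At an assumed r of 0.8 that is 0.632, giving 0.847 × 0.632 = 0.54 at n = 12 and 0.748 × 0.632 = 0.47 at n = 15.

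**The case against.** The labels do not decide whether an effect exists. They follow a set of tests at 5%, and the sentence opens with the effect size, so the results being interpreted are most naturally the effect-size results. This stands. A reader might infer that the labels replace the tests or create false-positive conclusions; the section does not support that.

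The rate of about 60% belongs to one definition of d and counts both directions. This also stands: for the water group alone it is about half, and with change over baseline SD and a high correlation it falls well below 60%. On that scaling, with r = 0.8, most or all medium labels would be significant, so it cannot be said in general that every small or medium label is compatible with no effect.

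The label is not uninformative throughout. Large occurs in 4% to 6% of cases with no effect, close to the test level, and in about 63% at the pilot-sized d of 0.93.

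A reader might also infer that the pilot gain changes label with the choice of SD. It does not. The gain is 625.1 - 566.2 = 58.9 m. On the pre SD it is 58.9 / 51.8 = 1.14; on the root mean square SD, sqrt((51.8² + 73.6²) / 2) = 63.6, it is 0.93; on the post SD, 58.9 / 73.6 = 0.80. All three are large.

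Finally, the contrast, the SD and the reporting of intervals are details that an article may leave to a fuller document. Their absence alone is not the point. What remains is that the stated rule reads magnitude off the point value, and at this sample size the point value cannot bear it.

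**Conclusion.** The point holds as one about interpreting magnitude. For a between-arm d at 12 to 15 per arm with no true effect, 57% to 61% of results would be labelled small or larger (29% to 31% in favour of the water group) and 18% to 23% medium or larger. Small labels and most medium labels would usually accompany a non-significant between-arm result; large labels are more trustworthy. These figures assume that d is scaled by the SD used in the test, and they are lower if change is scaled by baseline SD with a high pre-post correlation. The validity of the 5% tests is not affected. What changes is what may be said about the size of effects, across many outcomes in a small trial.

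**What to change.** Replace the label rule in the Analysis section as follows.

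- For each outcome, interpret magnitude from the between-arm difference in native units (metres for the 6MWT) with its 95% CI.
- If a standardised effect is also given, tie it to the between-arm contrast, name the SD, and report its 95% CI. Attach no verbal label to a point estimate alone.
- For outcomes analysed by rank tests, give a rank-based effect with a CI, such as the Hodges–Lehmann shift or the probability of superiority.

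This needs a few lines of text and routine software output, with no new data or participants. The downside is less flattering wording in the report.

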## Discussion

The objective of the DWR-IT program will be to investigate the influence of the 12-week DWR-IT program on body composition, functional capacity, and quality of life of overweight adults. DWR-IT can be very beneficial to the health of overweight people since it increases energy expenditure besides promoting positive effects on aerobic capacity and cardiovascular function and improvement of perception of quality of life and sleep in overweight and obese subjects submitted to training [32, 34]. It is believed that in addition to having the aforementioned outcomes, the DWR-IT program may be beneficial to the health of overweight middle-aged adults since the physical properties and the heated temperature of the water promote pain relief, reduction of joint overload, and low risk of musculoskeletal injuries [35–37].

Pasetti; Gonçalves; Padovani [37] subjected 30 obese middle-aged women to 12 weeks of DWR (47 min per session, three times per week, and water temperature between 28 °C and 29 °C) in two different modalities: continuous training (*n* = 12, 45.3 ± 6.3 years) with an intensity of 70–85% of resting HR and interval training (TI; *n* = 18; 46.6 ± 7.9 years) with an intensity between 70% and 75% of HR of rest. Body composition was assessed by using adipometry, and the World Health Organization Quality of Life BREF (WHOQOL-BREF) was used for quality-of-life analysis. After the aquatic training period, there was a reduction in body density and percentage of fat and improvement in quality of life in both types of training [37].

However, in spite of the benefits promoted by DWR, no randomized clinical trials on DWR-IT were found in the literature in the past five years that investigated functional capacity, muscle strength, sleep quality, or quality of life analyzed by a specific instrument for this population. In addition, in the aforementioned clinical trials, adequate methodologies for the control of the intensity of the aquatic exercises were not used since the physiological adaptations were not considered during immersion in the cardiovascular system, particularly in the HR. Finally, food consumption (pre- and post-intervention) was not recorded, a fact that may interfere in the responses of the variables related to body composition [37–40].

This study presents some strengths that in previous studies were not considered, such as the presence of the control group and use of specific instruments for the obese population. For the prescription of exercise intensity in the aquatic environment should take into account the help of HR for the prescription of intensity in the aquatic environment, thus avoiding cardiovascular overloaded of the control group, use of specific instruments for the obese population.

Therefore, the present study will provide clinical evidence that the DWR-IT program is effective in improving functional capacity, muscle strength, sleep quality, and quality of life in the obese. Thus, DWR is an alternative aquatic exercise to be considered by professionals in order to develop effective interventions for adults with obesity.

